#### Budget impact analysis

Using guidelines from the International Society for Pharmacoeconomics and Outcomes Research (ISPOR) [105], a budget impact analysis (BIA) will be performed to examine the financial consequences of implementing the eHealth PPI on a national level. In short, the analyses will be conducted from three stakeholder perspectives: [1] a societal perspective [2], a healthcare perspective, and [3] a healthcare insurer perspective. Within the societal perspective, healthcare costs and non-healthcare costs will be examined. Similar to the base-case analysis, healthcare costs will be estimated, using standard unit prices in Dutch healthcare [106]. For the other perspectives, national Dutch tariffs from Nationale Zorg Autoriteit (NZA) will be applied. For each stakeholder perspective, the following scenarios will be assessed: an eHealth PPI adoption rate of 40%, 60% and 80% among the target population. In addition, an extreme scenario will be modelled, assuming a 100% adoption rate. All scenarios will be compared to a base-case scenario, assuming a 0% adoption rate among the target population.

To explore these scenarios, a health-economic simulation model will be developed based on appropriate assumptions regarding the distributions of costs and effects. Costs will be modelled over the short term (12 months) and long term (36 months). Long-term costs will be discounted. Costs and outcomes will be extrapolated to a time horizon of 3 years for the target population. To address outcome uncertainty, sensitivity analyses with varying cost and discounting parameters will be conducted. To facilitate reproduction of the employed analyses, characteristics of each parameter (e.g., volumes, cost prices) and the model itself will be reported.

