#### Cost-effectiveness: base-case analyses

The probability of the two eHealth PPI conditions (arm 1 or arm 2) being cost-effective compared to TAU (arm 3) will be calculated from a societal perspective. Following the Dutch guidelines for economic evaluation in healthcare [65, 66], costs and effects extending beyond a 1-year follow-up period will be adjusted to their present value by an annual discount rate of 3% and 1.5%, respectively. In addition, all costs will be indexed to the most recent base year deemed appropriate. An additional scenario may be considered, assuming that costs and effects within and beyond the 1-year follow-up period should be adjusted to their present value. In addition to performing an ITT-analysis of cost-effectiveness, a complete-case cost-effectiveness analysis will be employed, using only data from participants who completed all measurements. Baseline differences in costs and outcomes between the trial arms will be analyzed and, if necessary, accounted for using regression analysis [101].

In the proposed cost-effectiveness analysis (CEA) and cost-utility analysis (CUA), the incremental cost-effectiveness ratio (ICER) will be calculated to facilitate two pairwise comparisons: (I) arm 1 vs. arm 3, and (II) arm 2 vs. arm 3. For both comparisons, the ICER represents the difference in societal costs between an eHealth PPI condition (arm 1 or arm 2) and the TAU condition (arm 3), divided by the corresponding difference in clinical outcomes (e.g., QALYs and MHC-SF scores). The robustness of the ICERs obtained will be assessed through non-parametric bootstrapping, using 1000 samples. This approach aims to predict the joint distribution of costs and effects within a cost-effectiveness plane (CE-plane) [102].

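### The main budget impact analysis discounts its 36-month costs, so the healthcare and insurer results are present values, not the amounts those payers would spend or save

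*Protocol article*

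**What the plan says.** The Protocol article, under Budget impact analysis, sets the aim "to examine the financial consequences of implementing the eHealth PPI on a national level". The analysis takes three perspectives: societal, then "a healthcare perspective, and [3] a healthcare insurer perspective". The two non-societal perspectives are priced at national Dutch tariffs. Adoption scenarios of 40%, 60%, 80% and 100% are compared with 0%.

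Costs are modelled over 12 months and over 36 months, and "Costs and outcomes will be extrapolated to a time horizon of 3 years for the target population". On discounting, the section says "Long-term costs will be discounted". It gives no rate, no start year and no layout by year. Sensitivity analyses will vary the cost and discounting inputs, but no undiscounted run is named.

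The only discount rates for the trial's economic results are under Cost-effectiveness: base-case analyses, where "costs and effects extending beyond a 1-year follow-up period will be adjusted to their present value by an annual discount rate of 3% and 1.5%," for costs and effects in that order.

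**The concern.** A budget impact analysis tells a budget holder how much money goes out or stays in, and when. Discounting answers another question: what a later amount is worth today. That second question is already handled in the cost-effectiveness and cost-utility analyses. If the same operation is applied to the 36-month budget figures, an insurer cannot set the year 3 result against its year 3 budget. A 36-month total likewise mixes year 1 money with reduced year 2 and year 3 money.

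The Discussion says that the results may inform resource allocation, so these figures are meant to be used. It also hopes that the intervention will reduce the number of later treatment sessions, which means cost first and savings afterwards. Discounting bears unevenly on such a stream: the early cost stays whole and the later savings are reduced.

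**Working it through.** The article reports no budget impact amount, so there is no figure of its own to reproduce. The check is how far discounting moves an amount due in each year.

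**Inputs**
- Horizon: 3 years (Budget impact analysis).
- Rate r: not given in that section. The 3% for costs comes from Cost-effectiveness: base-case analyses, and its use here is an assumption. A range of 1.5% to 5% is also assumed.
- Start: not given. Year 1 is taken as undiscounted, in line with the cost-effectiveness section's rule for costs beyond one year. This too is an assumption.

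**Formulas**
- Factor for year t: 1/(1+r)^(t−1).
- Shrinkage in year t: 1 minus that factor.
- Shrinkage of a level 3-year total: 1 − [1 + 1/(1+r) + 1/(1+r)²]/3.

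**At r = 3%**
- Year 1: factor 1.000.
- Year 2: 1/1.03 = 0.9709, shrinkage 2.9%.
- Year 3: 1/1.03² = 0.9426, shrinkage 5.7%.
- Level total: (1 + 0.9709 + 0.9426)/3 = 2.9135/3 = 0.9712, shrinkage 2.9%.

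**Other assumed rates**

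| Rate | Year 2 | Year 3 | Level 3-year total |
|---|---|---|---|
| 1.5% | 1.5% | 2.9% | 1.5% |
| 3% | 2.9% | 5.7% | 2.9% |
| 4% | 3.8% | 7.5% | 3.8% |
| 5% | 4.8% | 9.3% | 4.7% |

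**Other spending profiles at 3%**
- Rising 0.4 : 0.6 : 0.8: (0.4 + 0.6 × 0.9709 + 0.8 × 0.9426)/1.8 = 0.9648, shrinkage 3.5%.
- Front-loaded 0.6 : 0.3 : 0.1: 0.6 + 0.3 × 0.9709 + 0.1 × 0.9426 = 0.9855, shrinkage 1.45%.

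**If all three years were discounted at 3%:** the shrinkages would be 2.9%, 5.7% and 8.5%, and 5.7% for a level total.

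**Sign of the effect:** take an illustrative net stream of +1, −0.5, −0.5 (cost first, then savings).
- Undiscounted: 1 − 0.5 − 0.5 = 0.
- Discounted at 3%: 1 − 0.5 × 0.9709 − 0.5 × 0.9426 = +0.04.

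A cash-neutral programme would therefore appear as a small net cost. A percentage of the total has no useful meaning for a stream that changes sign.

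**The case against.** The strongest reply is that this is a stated choice and not a contradiction. Discounting in both analyses is internally consistent, and the guideline that the budget impact section cites is not available here to test it against. That stands, so the point rests only on the difference between cash and present value, judged against the purpose and perspectives that the article itself names.

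A second reply is that sensitivity analyses will vary the discounting and that the model and its parameters will be reported, so a reader could undo it. This helps only in part. No zero rate is named, and the main result stays discounted.

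A third reply is that the societal perspective has no single payer and no yearly budget. This stands, and it limits the point to the healthcare and insurer perspectives. A reader might infer that discounting is equally misplaced in all three perspectives, but the payer-budget argument does not clearly reach the societal one.

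Finally, the effect is small next to adoption scenarios that run from 40% to 100%, and the budget impact analysis is not among the economic objectives listed under Objectives. Both are true and bear on priority. Neither makes a present value into an outlay.

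**Conclusion.** The point holds for the healthcare and insurer perspectives. As planned, their main 36-month results would be present values and would not show what those payers spend or save. On the assumption of 3% from year 2, amounts shrink by 2.9% in year 2 and 5.7% in year 3, and a level 3-year total by 2.9%. The 12-month result is unaffected if year 1 is undiscounted.

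A reader might go further and infer that the yearly amounts shown to payers will always lie below what they would actually pay. The document does not support that. It fixes no rate, start year or yearly table, and the direction depends on the stream: later net costs are understated, but so are later net savings. With up-front cost and later savings, the net 3-year result moves the other way and looks more expensive than it is.

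The effect is modest, but it is systematic and more data would not remove it. It does not touch the trial's effectiveness or cost-effectiveness conclusions.

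**What to change.** In the budget impact analysis, for the healthcare and insurer perspectives, make undiscounted costs for each of years 1, 2 and 3 and their sum the main result in every adoption scenario. Keep a discounted 3-year total as a labelled sensitivity analysis, with its rate and start year stated. For the societal perspective, show the undiscounted figures beside the discounted ones. Leave discounting in the cost-effectiveness and cost-utility analyses as it is.

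This takes a sentence or two in the analysis plan and some extra columns in the results tables. It needs no new data and no change to the simulation model beyond setting the discount rate to zero.

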### Implementation procedures

#### Quantitative and qualitative analyses

In accordance with the aforementioned framework for eHealth evaluation [89], advanced mixed methods will be used to inform an evaluation of eHealth PPI implementation procedures. In addition to analysing participants’ quantitative post-module ratings using descriptive statistics (e.g., means, frequencies, standard deviations), participants’ qualitative responses to the post-module process questions will be summarized using thematic analysis with coding trees in both studies, until data saturation is reached [107]. In study 2, an Analysis Of Variance (ANOVA) may identify differences in eHealth PPI login frequency data (i.e., adherence and engagement) and SUS outcomes (i.e., feasibility and accessibility) across the RCT arms, while correlation and regression analyses may explore the associations between SUS outcomes, eHealth PPI login frequencies, the primary outcome (i.e., MHC-SF), and secondary outcomes. Data on all aforementioned procedural constructs may potentially explain variations in preliminary intervention effects (study 1) and (cost-)effectiveness outcomes across RCT conditions (study 2). Therefore, triangulation of quantitative and qualitative data will be considered in both studies [108]. Different PPI starting times between patients and loved ones are anticipated in both studies (e.g., due to a delay in obtaining consent from the patients’ loved ones), which may particularly affect SUS outcomes representing the intervention’s accessibility and feasibility. Therefore, average differences in PPI starting time between patients and loved ones (study 1) and across the RCT arms (study 2) will be assessed using an ANOVA. If significant differences in PPI starting time are found, SUS outcomes will be examined using regression modeling, employing the PPI starting time as a covariate.

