## Objectives

Two experimental conditions will be established involving the eHealth PPI during the waiting period for [1] patients only and [2] for patients and their loved ones. Primarily, both experimental conditions will be compared to a [3] treatment as usual (TAU) condition, involving patients who will not receive the eHealth PPI during their waiting period. However, conditions 1 and 2 will also be compared to each other exploratively. In all three conditions, patients will receive a mental health treatment as usual after the waiting period. Using these three RCT conditions and a small pilot study (replicated single-case design), the study protocol will address objectives and hypotheses from three areas of expertise:

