##### System Usability Scale (SUS)

While feasibility refers to the perceived usability and functionality of the eHealth PPI, accessibility examines participants’ ease of access to the eHealth PPI, considering technological literacy [91]. The System Usability Scale (SUS) [92], which is a 10-item questionnaire assessing the perceived usability of digital tools using an ordinal 5-point Likert scale ranging from ‘’strongly disagree’’ to ‘’strongly agree’’, will be used to measure feasibility and accessibility in both studies. The SUS was initially developed to examine adult populations interacting with digital tools. With a Cronbach’s alpha of 0.74, a Dutch version of the SUS was considered internally consistent and reliable for usability assessment [93].

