##### Login frequency data

To further explore the accessibility of the eHealth PPI, differences in PPI starting time among participants (i.e., the time between providing informed consent and starting the first PPI module) will be measured in both studies using login frequency data from the eHealth platform. Adherence, defined as the extent to which study participants comply with the basic eHealth PPI protocols (i.e., moving through all required tabs within a module and finishing digital homework assignments), will also be measured in both studies using login frequency data. Lastly, the same login frequency data aims to measure engagement in both studies, defined as the depth of interaction between study participants and the modules of the eHealth PPI. In this context, engagement is measured by assessing both the total time spent on each PPI module and the interactions between study participants and the optional drop-down menus within each PPI module, including additional information and homework assignments.

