## Data analysis

All analyses of (cost-)effectiveness will be performed in accordance with the Intention-To-Treat (ITT) principles, meaning that data from all participants will be analysed according to the study condition to which they were initially assigned, regardless of adherence [94]. Assessment of baseline inequalities between study conditions will be performed and followed up, if needed. Due to the longitudinal nature of study 1 and study 2, dropout and other processes causing missing data are expected [95]. Appropriate missing data handling techniques will be applied after assessment of the magnitude, mechanisms, and patterns of missing data [96]. A one-sided alfa of 0.05 will be applied in both studies. Since multiple comparisons between RCT arms will be performed in study 2, this significance level of 0.05 will be adjusted to manage Type I error probability, using the Holm-Bonferroni method [97].

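### PPI starting time, an additional exploratory accessibility measure, is compared by ANOVA among starters only, so differences in uptake go unseen and slow groups that give up can look faster

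*Protocol article*

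**What the plan says.** Under Login frequency data, the protocol article introduces the measure with these words: "To further explore the accessibility of the eHealth PPI, differences in PPI starting time among participants". It defines the measure as "the time between providing informed consent and starting the first PPI module". Under Quantitative and qualitative analyses, average differences in starting time are compared between patients and loved ones in study 1; in study 2 the differences "across the RCT arms (study 2) will be assessed using an ANOVA". The result has one stated use: "If significant differences in PPI starting time are found, SUS outcomes will be examined using regression modeling", with starting time as the covariate.

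Four other statements bear on the point.
- The System Usability Scale (SUS) is the other accessibility measure; it "will be used to measure feasibility and accessibility in both studies". Table 2 places it at T1, after PPI completion.
- The TAU arm is described under Objectives as "involving patients who will not receive the eHealth PPI during their waiting period", so it has no starting time.
- The intention-to-treat rule is limited in scope: "All analyses of (cost-)effectiveness will be performed in accordance with the Intention-To-Treat (ITT) principles".
- The missing-data rule is general: "Appropriate missing data handling techniques will be applied after assessment of the magnitude, mechanisms, and patterns of missing data".

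The article does not say how people who never open the first module enter the starting-time comparison. It names no measure of the proportion who start.

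**The concern.** Starting time is a time to an event that some participants will never reach. As defined, it has no value for them, and an ANOVA of averages has no place for a participant without a value. Never starting is information about access: it means that the event did not occur in the period observed. It is not an ordinary missing score.

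Two things can follow. Groups with the same delay among starters but different uptake will look alike. If those who would have started late are the ones who give up, removing them shortens the mean among starters, and the group with worse access can look faster. At stake is how one measure in the exploratory implementation evaluation is read. The Discussion itself expects low eHealth literacy to compromise adherence, and people with that barrier are plausible non-starters.

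**Working it through.** **Inputs from the protocol article.** The definition, the ANOVA and the absence of a starting time under TAU are quoted above. The group size comes from A priori sample size: 207/(1 − 0.355) = 320.9, rounded up to 321, and 321/3 = 107 patients per arm. The plan gives no figure for uptake or starting time, so there is nothing of its own to reproduce.

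**Assumptions for illustration.** Arm 1 vs arm 2, 107 patients each. The latent delay T is exponential with mean 2 weeks. Everyone starts in arm A. In arm B a fraction q of those with T > 2 weeks never start. One-way ANOVA on starters at 0.05, 4,000 simulated trials. (The protocol's alpha of 0.05 is one-sided; an F test has no direction.)

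**Formulas, same latent delay in both arms.** P(T > 2) = e^(−1) = 0.368. E[T; T > 2] = (2 + 2) × 0.368 = 1.472.
- Share starting in arm B = 1 − 0.368q.
- Mean among starters in arm B = (2 − 1.472q)/(1 − 0.368q).

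| q | Share starting, arm B | Mean among starters, arm B (arm A: 2.0) | ANOVA significant in favour of arm B (simulated) |
|---|---|---|---|
| 0 | 100% | 2.0 weeks | 2% |
| 0.25 | 91% | 1.80 weeks | 11% |
| 0.50 | 82% | 1.55 weeks | 39% |
| 0.75 | 72% | 1.24 weeks | 85% |

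The simulated shares and means agree with the formulas.

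**Arm B truly slower.** Let its latent mean be 2.5 weeks. Then P(T > 2) = e^(−0.8) = 0.449 and E[T; T > 2] = (2 + 2.5) × 0.449 = 2.022. With q = 0.75:
- share starting = 1 − 0.75 × 0.449 = 66%;
- mean among starters = (2.5 − 0.75 × 2.022)/0.663 = 1.48 weeks, against 2.00 in arm A.

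The slower arm was significantly favoured in about 45% of simulated trials. With q = 0.50, about 78% start, the mean is about 1.92 weeks, and the slower arm is favoured in about 5%. The reversal therefore depends on how strongly giving up is tied to delay.

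**Non-start unrelated to delay.** With 10%, 30% or 50% of one arm never starting at random, the mean among starters is unbiased and the ANOVA rejects in 5.0%, 4.9% and 4.4% of trials. That is its error rate: the loss is not seen at all.

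**What a comparison of proportions would show.** With 107 per arm, two-sided 0.05, and assumed uptake of 95% vs 85%: [0.10 − 1.96 × √(2 × 0.90 × 0.10/107)] / √((0.95 × 0.05 + 0.85 × 0.15)/107) = (0.1000 − 0.0804)/0.0404 = 0.485, a power of 69%. For 95% vs 65% the power is over 99%.

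**The case against.** The strongest reply is that this is a minor process measure in a condensed article. The implementation aim is only to explore, no hypothesis is attached, and missing-data handling is deferred in general terms. In the analysis section the ANOVA serves to decide on a covariate for the SUS; it gives no verdict on access. A usability score means little for someone who never opened the platform, so starters are the right group for that decision.

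Much of this stands. A reader might infer that the SUS adjustment rests on the wrong data; it does not, and that step needs no change. A reader might also infer that starting time is the trial's accessibility outcome, or that non-starters vanish from the evaluation. The documents support neither. The SUS is the other named accessibility measure, and login data are also used for adherence and engagement, where a non-starter could appear with zero activity. The article does not say whether such zeros are counted. Nor does it assign a patient versus loved-one test to study 2; it names that comparison for study 1, which has five of each.

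The reply does not remove the core point. The article fixes both the definition and the method, so this is a stated choice and not a detail left open. The intention-to-treat sentence does not reach process measures. The SUS is collected after the PPI, and adherence would mix non-starters with people who started and stopped.

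**Conclusion.** The point holds as a low-priority improvement. The planned comparison of starting time describes starters only. Differences in uptake are invisible to it, and if slow participants are also those who never start, the ordering of the groups can reverse.

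A reader might go further and conclude that the ANOVA will make poor access look good. The documents do not support that. A reversal needs non-start to be related to delay and to differ between groups; otherwise the loss is hidden, not reversed. In the illustration, the share of trials favouring the worse arm runs from 11% to 85%, according to how many slow participants are lost. All of these figures rest on assumed uptake and an assumed exponential delay. The effect is confined to one exploratory accessibility measure; the primary MHC-SF analysis is untouched.

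**What to change.** For study 2:
- Report the number and proportion who started among all consenting participants assigned the PPI: patients in arm 1, patients in arm 2, and loved ones in arm 2.
- Analyse time from informed consent, the protocol's own origin, to the first module. Use Kaplan-Meier curves and a log-rank or Cox comparison of arm 1 with arm 2. State that TAU has no starting time.
- Censor non-starters at a stated end of the access period. The article says that the modules are offered over eight weeks but not when access closes, so this date has to be fixed.
- Report patients and loved ones descriptively in the same way.
- Keep starting time as a SUS covariate among starters, as planned.

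The cost is a change of analysis wording and slightly more analysis work. The consent and first-module times are already needed for the planned measure; the only addition is to keep everyone assigned the PPI in the denominator.
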